***Behavioral Outcome Measures:***

Outcome measures were categorized into (1) Compliance measures’ (number of training sessions and compliance with the required training intensity as quantified by the Cogmed Improvement Index score); (2) ‘Criterion measures’ (closely resembled tasks trained in WM program); (3) ‘Near transfer” measures (indices of other cognitive functions or measures of WM that differed from the trained tasks); and (4) ‘Far transfer’ measures (indices of academic achievement and self-report questionnaires). These measures were selected based on the results of previous studies ([24](#_ENREF_24), [25](#_ENREF_25)).

***Compliance measures***

Three measures will be used: i) Number of training sessions completed; ii) Mean proportion actively engaged in training while logged in, as recorded by the software program; and iii) the Cogmed Improvement Index score, which is computed automatically from two training indices (Start Index, Max Index) and provided for every user. The Start Index is calculated with the results from days 2 and 3, and the Max Index is calculated with the results from the two best days during the training period. The Improvement Index is calculated by subtracting the Start Index from the Max Index. The mean Improvement Index for individuals aged 18 to 65 years is 29 (normal range 15-41). Higher Index scores signify good compliance and effort with the training.

***Criterion Measures*** (similar to the trained WM activities)

i) Auditory-Verbal WM: Two measures are to be used. The Digit Span subtest from the *Wechsler Adult Intelligence Scale- Fourth Edition* (WAIS-IV) ([26](#_ENREF_26)) and the *‘Add-3’* WM test that requires participants to add ‘3’ to each digit in a set of 4 digits presented at a constant rate (e.g., the response to the set ‘3 1 5 4’ should be ‘6 4 8 7’ ([27](#_ENREF_27))

ii) Visual-Spatial WM: Two measures are used. The *Cambridge Neuropsychological Testing Automated Battery* *Spatial Span task* was used to assess visual-spatial WM (CANTAB) ([28](#_ENREF_28)) and the ‘*Finger-Windows’* subtest from the *Wide Range Assessment of Memory and Learning* ([29](#_ENREF_29)). The CANTAB task presents a set of white squares on a screen, which momentarily change colour in a variable sequence. The participant must then touch the boxes in the same order that they changed colour on the screen. Task demands intensify, as the number of boxes is increased from two to nine. However, if the participant makes an error, the next trial remains at the same difficulty level. Spatial span scores range from 0-9, with the score representing the highest level at which the participant reproduces at least one correct sequence.

***Near-Transfer Measures*** (other cognitive measures that differ from trained activities)

Four measures are used. The *CANTAB Spatial Working Memory task* is to be used to differentiate and quantify WM memory and strategy skills. Based on the self-ordered pointing task ([30](#_ENREF_30)) , it differs from WM span tasks because it is not affected by varying levels of dopamine in the dorsolateral prefrontal cortex ([31](#_ENREF_31)). Participants are required to update information about spatial locations in working memory: they must search boxes to find the hidden token, but must not return to the same box where a token has already been found. There are four trials for each of three load conditions (four, six and eight boxes). Performance was measured according to the number of errors made. At the end of the task, subjects received a strategy score: a low score indicates efficient strategy use, whereas high scores reflect poor strategy use.

*CANTAB Stockings of Cambridge (planning)*

The subject is shown two displays, each containing three balls, with each set arranged in different “stockings” hanging in three pockets. The subject must move the balls in the lower display to copy the pattern in the upper display. This involves working out an optimal set of moves (the fewest moves possible) and then executing them by moving one ball at a time.

*A Quick Test of Cognitive Speed* (AQT) consists of three rapid naming tasks (colour, form, color-form) and measures processing speed, cognitive set shifting between visual dimensions and semantic fields, and activation of working memory for processing and monitoring ([26-29](#_ENREF_26)).

*Behavioural Assessment of the Dysexecutive Syndrome (BADS).* This validated assessment battery assesses executive function in everyday life that consists of 6 independent tasks; it is sensitive to mild cognitive impairment in adults as well as more severe impairment ([32](#_ENREF_32), [33](#_ENREF_33)). We will use two of the tests: Rule Shift Cards and Zoo Map.

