The study uses a randomized controlled design in which participants are randomly assigned to one of three groups: standard-length version of high-intensity WM training, a novel shorter version of the high-intensity WM training, or a wait-list control group. The standard-length WM training group will undergo 25 training sessions for 30 min/day, 5 days a week for 5 weeks and receive weekly phone calls from a cogmed coach to review progress and adjust the training as needed; the group assigned to the shorter version of the high-intensity training will also undergo 25 training sessions but for just 15 min/day, 5 days per week for 5 weeks and also receive the same type of weekly phone calls from a cogmed coach; and the wait-list group will not undergo any WM training during the 5 week period but will receive weekly phone calls from a member of the research team to review progress and advice on time management, organization, and mnemonic strategies. All groups will undergo pre testing, testing three weeks following completion of training and again at three-month follow-up. The wait-list group will be offered the cogmed training after the follow-up assessment. We will also recruit a group of healthy age- and gender-matched peers who will be assessed once and will not undergo WM training; this comparison group allows us to determine initial group differences in behavioral and neural indices of WM and whether WM training normalizes these indices in the ADHD groups.

*Diagnostic screening measures* (Baseline assessment only for AHD/LD and healthy controls).

All participants must have received a prior diagnosis of ADHD/LD to register with the college/university Student Disability Services. Since there is no standardized assessment used by Student Disability Services, we will administer a brief interview and standardized rating scales and screening tests to quantify the current symptoms of ADHD, and other clinical problems such as mood and stress levels.

*Adult ADHD Self-Report Scale* (ASRS v1.1) is a reliable and valid scale for evaluating ADHD in adults ([20](#_ENREF_20), [21](#_ENREF_21)). The ASRS v1.1 is an instrument consisting of eighteen questions based on the criteria used for diagnosing ADHD in adults using DSM-IV-TR criteria. Questions focus on how often ADHD symptoms occur (0=never, 1=rarely, 2=sometimes, 3=often, 4=very often). Scores for each item are added to calculate a total score.

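### The Cogmed Improvement Index measures gain on the trained tasks, so it should not be reported as a measure of compliance

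*Protocol*

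**What the plan says.** Section 12 deals with compliance in two places.

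- Under Behavioral Outcome Measures, the compliance category has two parts: the number of training sessions, and "compliance with the required training intensity as quantified by the Cogmed Improvement Index score". The Index is the only quantifier of intensity named there.
- Under Compliance measures there are three. The first two are "i) Number of training sessions completed; ii) Mean proportion actively engaged in training while logged in, as recorded by the software program". The third is the Improvement Index.

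The Index is then defined. Its starting value comes from days 2 and 3, its maximum from whichever two days went best, and "The Improvement Index is calculated by subtracting the Start Index from the Max Index". The protocol gives reference values by age only (mean 29, normal range 15 to 41, ages 18 to 65) and adds the interpretation: "Higher Index scores signify good compliance and effort with the training".

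**The concern.** Compliance describes what a participant did: sessions attended, time spent working, trials completed. The Index contains none of these. It is the difference between two performance levels, so it describes what the training did to the participant. Labelling it compliance mixes exposure with response.

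Two consequences follow if the text is applied as written. First, non-response is reported as poor compliance in a listed outcome category, which could be used to explain away a null result. Second, section 11 asks as objective ii whether lower-intensity training also improves working memory. If the shorter version yields less gain, its lower Index would be read as weaker adherence, and the finding and its excuse would be the same number.

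**Working it through.** The protocol states no calculation on this point, so there is no figure to reproduce. The check is of definitions first, then an illustration.

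**Definitions.** Index = Max (two best days) − Start (days 2 and 3). Neither term counts sessions, minutes or trials. Attendance enters only indirectly, because more days give more chances for a high score and more time to learn.

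**Planned exposure (section 12, Study Design).** For the longer arm: "The standard-length WM training group will undergo 25 training sessions for 30 min/day, 5 days a week for 5 weeks". The shorter arm has the same 25 sessions at 15 minutes.
- Longer: 25 × 30 = 750 min. Shorter: 25 × 15 = 375 min.
- The arms differ in minutes per day and not in the number of days from which the best two are chosen.

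**Illustration.** All of the following are assumptions, not protocol figures: simple two-day means; independent normal daily noise; true gain G in index points; learning curve c(d) = G(1 − e^(−(d−1)/8)) / (1 − e^(−3)) for day d; and missed sessions falling at the end.

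1. *No learning.* The expected Index is the mean of the two highest of K standard normal scores, times the daily SD: 0.83 SD for K = 5, 1.27 for K = 10 and 1.74 for K = 25. At 25 sessions and SD 3, 5 or 7 this is 1.74 × 3 = 5.2, 1.74 × 5 = 8.7 and 1.74 × 7 = 12.2. Picking the best days gives a positive score with no learning at all.

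2. *Same attendance, different response.* With 25 of 25 sessions and SD 5, simulated means are 8.7, 18.7 and 30.1 for G = 0, 15 and 30. Identical attendance runs from below the 15 to 41 range to about the quoted mean of 29.

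3. *Less attendance, higher score.* With SD 5, G = 30 and 15 sessions the mean is 23.9; with G = 15 and all 25 sessions it is 18.7. The order does not depend on the noise. Setting it to zero:
   - G = 30, 15 sessions: best days (25.36 + 26.09)/2 = 25.72; start (3.71 + 6.98)/2 = 5.35; Index 20.4.
   - G = 15, 25 sessions: best days (14.90 + 15.00)/2 = 14.95; start 5.35/2 = 2.67; Index 12.3.

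4. *The Index does carry some attendance information.* With G = 30 and SD 5 it averages 7.1, 17.7, 23.9, 27.6 and 30.1 after 5, 10, 15, 20 and 25 sessions.

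5. *Between arms, at full attendance in both.* Start from 30.1 (G = 30, SD 5). If shorter sessions only make daily scores noisier (SD 5 × √2 = 7.07, assuming half the trials), the mean rises to 33.0. If they only halve the gain (G = 15), it falls to 18.7. The sign depends on which assumption is made.

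**Trial counts (section 12, Intervention).** One sentence requires 90 trials per training day. The typical plan is 15 trials of each of 8 tasks, 8 × 15 = 120. No count is given for the 15-minute version.

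**The case against.** The strongest reply is that little rests on the Index. Two of the three measures under Compliance measures record adherence directly, so a fast learner who skips sessions would be exposed by the session count. The protocol sets no compliance threshold, and 15 to 41 is called a normal range, not a cut-off. The planned analyses are repeated measures ANOVA (section 12) and intention to treat with last observation carried forward (section 22). The Index also rises with sessions completed.

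All of this stands, and it rules out three stronger readings that a reader might infer.

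- *That compliance rests on the Index alone.* It does not. The Index is the sole quantifier only of intensity, and only under Behavioral Outcome Measures.
- *That participants will be classed as compliers by the Index, so that training looks effective among them by construction.* No complier, per-protocol or dose-response analysis is described.
- *That the Index is biased between the two arms by a known amount.* Both arms have 25 sessions, no comparison of the Index between arms is stated, no daily SD is given, and the assumed shifts point in opposite directions.

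The reply does not rescue the interpretive sentence. The protocol itself fixes the meaning of a high score, and that meaning does not follow from the definition two sentences earlier.

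**Conclusion.** The point holds in limited form. One of three compliance measures is a gain score, and the statement that a high value shows good compliance is wrong as written. This follows from the definition and needs no assumption.

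The sizes in the illustration depend on the assumed curve, gains and SDs, and show only that the problem can be large on the Index's own scale: about 21 points (30.1 − 8.7 = 21.4) between full attenders who differ only in response. No between-arm size or direction can be claimed. No planned efficacy analysis is invalidated. What is affected is what the trial may say about compliance, and whether a weaker gain in the shorter arm can be told apart from poorer adherence.

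**What to change.** In both places in section 12:

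- Take compliance from the logged process measures: sessions completed out of 25, and the share of logged-in time spent actively training, each judged against that arm's own plan. List the same measures under Behavioral Outcome Measures and Compliance measures.
- Move the Improvement Index to a separate descriptive heading such as training-task gain, and delete the sentence that equates higher scores with compliance and effort.
- Add trials completed as a further process measure only after the 90 and 8 × 15 = 120 daily trials are reconciled and the planned count for the 15-minute version is stated.

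The first two changes are wording only, since both process measures are already listed for collection. The third needs a decision on the trial counts by those responsible for the intervention.

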***Far-Transfer Measures***

*ASRS v.1.1* . This scale will also be used as an outcome measure at post-test and follow-up to ascertain any change in ADHD symptoms ([20](#_ENREF_20), [21](#_ENREF_21)).

*Cognitive Failures Questionnaire (CFQ).* This tool measures self-reported failures in perception, memory, and motor function in every day life. This 25-item scale has good external validity ([34](#_ENREF_34)). Questions require subjects to rank how often these mistakes occur (0=never, 1=very rarely, 2=occasionally, 3=quite often, 4=very often). Scores for each item are added to calculate a total score.

*Barkley Deficits in Executive Functioning Scale (BDEFS).* This questionnaire tool will be used to evaluate dimensions of adult executive functioning and working memory in daily life ([35](#_ENREF_35), [36](#_ENREF_36)). We will use the short form.

***Neuroimaging Outcome Measures:***

Three well-validated measures of working memory and related processes will be administered in the EEG lab at OISE, adjacent to the cognitive lab where the behavioral measures are administered.

Go-nogo task (response inhibition)

The subject is shown sequences of letters and instructed to press a button whenever a letter shows up on the screen, but to withhold a response whenever a letter occurs twice in a row. This task will take 8 minutes and is adapted from Garavan, Ross, & Stein (1999).

Delayed Working memory task (working memory)

The subject is shown sequences of either 2 (low load) or 4 (high load) shapes. After a delay period of two seconds, a probe appears and the participant needs to respond by pressing a button whether the probe stimulus was part of the sequence shown before or not. This task will take 16 minutes and is adapted from Haenschell et al., (2007).

Selective Working memory task (selective attention + working memory)

The subject is shown an array of small colored squares to different parts of their visual field. This memory array will consist of either 2 (low load), 4 (high load), or 2 (low load + 2 ‘distractor’ circle) items. After a delay, a test-array is shown and the participant is to respond whether the test-array matched the memory array. This task will take 24 minutes and is adapted from Vogel, McCollough, & Machizawa (2005).

*Imaging equipment*

EEG (Electroencephalography) will be recorded using a 128-channel Geodesic Sensor Net (Tucker, 1993). The net consists out of sponges which contain sensors which allow the measurement of brain activity on the surface of the head.

The basic approach to tests the effects of the training program will be to use repeated measures ANOVA. Separate analyses will be conducted for the primary, secondary and tertiary outcome measures.

For the imaging, raw EEG will be sampled at 500 Hz, using EGI software (Electrical Geodesic, Inc., Eugene, OR) and further processed using EGI software (Electrical Geodesics, Inc., Eugene, OR) after which ERP (Event Related Potential: averaged brainwaves) measures will be created and analyzed in SPSS. Repeated measures ANOVA’s will be used to compare levels of brain activity in various regions before and after training.

**13. PARTICIPANTS OR DATA SUBJECTS**

The sample will include college students with ADHD and/or Learning Disabilities attending the University of Toronto, York University, Humber, Ryerson, or George Brown. The estimated sample size is 160 participants (40 in experimental, 40 in low intensity, 40 in waitlist, and 40 normal healthy controls). Participants will be of no relationship to the investigators. Those who participate in the study must be enrolled as full time students. All participants must have received a previous diagnosis of ADHD and/or a Learning Disability. Exclusionary criteria will include uncorrected sensory impairment, evidence of a neurological dysfunction or a history of psychosis. Personal information, and checks on eligibility, will be obtained directly from the participants during the intake procedures which are appended to this proposal. Ethics approval will be sought for institutions other than the University of Toronto in accordance with those institutions’ policies and procedures.

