**Please include a list of appendices for all additional materials submitted.**

**11. RATIONALE**

Attention-Deficit/Hyperactivity Disorder (ADHD) and Learning Disability (LD) are among the most common neurobehavioural disorders, with prevalence rates estimated at about 5% to 9% ([1](#_ENREF_1), [2](#_ENREF_2)). Approximately 4% of youth in the United States have a comorbid diagnosis of ADHD and a Learning Disability (ADHD/LD) ([3](#_ENREF_3)). Research has shown ADHD/LD symptoms persist into young adulthood, a time when many are enrolled in post-secondary education. Students with ADHD/LD at the post-secondary education level constitute an emergent subgroup of the ADHD and LD populations that have received far less attention in the literature compared to children, adolescents and employed adults. The actual percentage of college students with ADHD/LD is unknown; however, some estimates suggest that 2-8% of students attending post secondary education have ADHD, LD or both (3). Youth with the additive problems of both disorders are at high risk for academic failure, and poor psychosocial and occupational outcomes in adulthood ([3](#_ENREF_3)). The “multiple deficit model” suggests that there is a common genetic and neuropsychological underpinning to these disorders ([3](#_ENREF_3)). For example, ADHD and LD share similar features, such as core deficits in processing speed and working memory ([4](#_ENREF_4), [5](#_ENREF_5)). ADHD and LD are each associated with several cognitive difficulties including poor working memory (WM) and processing speed ([4](#_ENREF_4), [5](#_ENREF_5)). WM is a “mental workspace” that provides temporary storage and manipulation of information and is closely related to *g*, a proposed measure of general cognitive ability ([6](#_ENREF_6)). In addition, WM has also been found to predict academic achievement ([7-9](#_ENREF_7)). One major problem is that current intervention approaches for ADHD/LD do not target the underlying cognitive deficits fundamental to these diagnoses. Thus, interventions that address underlying cognitive difficulties, such as WM, are a promising avenue of additional treatment for youth with combined ADHD/LD.

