WM capacity has generally been thought to be a fixed trait, but recent studies have suggested that it can be improved by intensive and adaptive computerized training ([10](#_ENREF_10)). This intervention approach has been evaluated in children and adolescents with ADHD, older adults, and adult stroke patients and shown promising results ([11-14](#_ENREF_11)). Subjects not only improved on the trained WM tasks, but some of the studies suggest that improvements may generalize to non-trained WM activities, complex reasoning tasks, academic functioning, and behavioral symptoms of ADHD or working memory failure ([11](#_ENREF_11), [15](#_ENREF_15)). Moreover, brain imaging studies have provided converging evidence of training-related improvements in working memory: specifically increased activation has been found in cortical regions implicated in working memory ([14](#_ENREF_14), [16](#_ENREF_16), [17](#_ENREF_17)). However, no studies to date have investigated whether WM capacity can be improved in a population of young adults with ADHD/LD enrolled in post-secondary education programs. Nor have the results been replicated or elaborated upon using different imaging methodologies, like EEG (Electroencephalography), which is able to capture the millisecond time parameters of cognitive processing and so may provide new insights into the neural mechanism of WM and effects of WM training.

The overall objective of the current study is to determine the effectiveness of WM training, as administered by community-based psychologists licensed to provide this training, for college students with ADHD/LD. Specific objectives are to determine whether; i) high-intensity computerized WM training enhances WM capacity in college students with ADHD/LD, using behavioural as well as neuroimaging indices of change; ii) lower-intensity training would also result in improvements in WM; iii) WM training normalizes WM, as compared to typically developing peers (i.e., a healthy comparison group of college students); iv) improvements in WM will generalize to secondary outcome tasks, such as inhibitory control and planning; v) WM training will also ameliorate ADHD symptoms of inattention and hyperactivity; and vi) improvements will be sustained for at least a few months after completing the training.

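### The protocol defines its population inconsistently: comorbid ADHD/LD in the rationale, either diagnosis alone at entry, so the ADHD-symptom test includes students not selected for ADHD

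*Protocol*

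**What the plan says.** The protocol describes its population in several ways.

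- **Section 11, Rationale.** The abbreviation is introduced for young people who "have a comorbid diagnosis of ADHD and a Learning Disability (ADHD/LD"), and the argument ends by saying that such interventions "are a promising avenue of additional treatment for youth with combined ADHD/LD". The same section also gives a prevalence estimate that "2-8% of students attending post secondary education have ADHD, LD or both".
- **Section 11, objectives.** The overall aim is set "for college students with ADHD/LD. Specific objectives are to determine whether" six things hold. The fifth is that "WM training will also ameliorate ADHD symptoms of inattention and hyperactivity".
- **Section 12, Methods.** The entry statement under the diagnostic screening measures reads "All participants must have received a prior diagnosis of ADHD/LD to register with the college/university Student Disability Services". Just before it, in the study design, the randomised students are called ADHD groups in the comparison with healthy peers.
- **Section 13, Participants.** "All participants must have received a previous diagnosis of ADHD and/or a Learning Disability". The and/or wording also appears in that section's opening sentence.

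No exclusion criterion in section 13 removes students without ADHD. In section 12 the ASRS serves to quantify current symptoms, with no cut-off for entry, and it is listed again as a far-transfer outcome without restriction to students with ADHD. Allocation is random to three arms, with no stratification mentioned. The planned size is 40 in each of four groups.

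**The concern.** Read literally, section 13 admits three kinds of student: ADHD only, LD only, and both. Only the third matches the term as section 11 introduces it, and LD-only students do not fit the Methods label of ADHD groups. Two things follow.

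First, it is unclear to whom the result applies. The objectives are set for ADHD/LD, but the sample would be a mixture whose proportions the protocol neither fixes nor predicts. The comparison with healthy peers (objective iii) also depends on who is in the randomised groups.

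Second, objective v asks whether training reduces inattention and hyperactivity. LD-only students were not selected for those symptoms and may have less room to improve on the ASRS. If so, including them shrinks the average difference between arms, in a trial with only 40 per arm.

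**Working it through.** **Step 1: can the passages be read together?** An LD-only student is eligible under section 13. The same student is not comorbid as section 11 introduces the term, and is not in an ADHD group as Methods uses the phrase. The Methods entry sentence could be read either way, because a slash can mean *and* or *or*. No single reading fits all the passages, so the conflict is in the text and needs no outside figure.

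**Step 2: the protocol's own number.** 4 × 40 = 160, which reproduces the stated total. The protocol gives no effect size, SD, alpha or power, so there is no power figure to reproduce.

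**Step 3: how large could dilution on the ASRS be?** The documents supply n = 40 per arm. Everything else here is assumed: a two-sided 5% test, a benefit of 0.50 SD in students with ADHD, baseline–outcome correlation 0.6, LD-only share *q*, and LD-only benefit equal to a fraction *b* of the ADHD benefit. Any change in variance from mixing diagnoses is ignored.

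- Average effect in all randomised: 0.50 × [1 − q(1 − b)].
- Baseline-adjusted comparison: residual variance factor 1 − 0.6² = 0.64, so the effect is divided by √0.64 = 0.8.
- Noncentrality: (effect / 0.8) × √(n/2), with 2n − 2 degrees of freedom. With no LD-only students this is 0.625 × √20 = 2.80 on 78 df, and power is 78.8%.

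| LD-only share | Effect, b = 0 | Power, b = 0 | Effect, b = ½ | Power, b = ½ | ADHD-diagnosed subset: n per arm, power |
|---|---|---|---|---|---|
| 20% | 0.40 | 59.8% | 0.45 | 70.0% | 32, 69.2% |
| 33% | 0.33 | 45.2% | 0.42 | 63.3% | 27, 61.6% |
| 50% | 0.25 | 28.2% | 0.375 | 54.4% | 20, 48.7% |

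With no LD-only benefit, the subset has more power than the full set in each row. With half the benefit the order reverses in each row.

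**Step 4: sensitivity to the analysis.** Section 12 plans repeated measures ANOVA. With one pre and one post measurement, its group-by-time test is a test of change scores, with variance factor 2(1 − 0.6) = 0.8 in place of 0.64. Undiluted power is then 69.5%. At 20%, 33% and 50% LD-only it is 50.6%, 37.7% and 23.5% with no benefit in them, and 60.3%, 53.9% and 45.7% with half. The levels are lower and the pattern is the same.

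**Step 5: chance imbalance.** With one-third LD-only and unstratified allocation, the 95% limit for the difference in LD-only share between two arms is 1.96 × √(2 × ⅓ × ⅔ / 40) = 0.207, about 21 percentage points.

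**The case against.** The strongest reply is that the contradiction is mild. Section 11 itself uses the looser wording in its prevalence estimate, the slash in Methods is ambiguous, and section 13 is the explicit statement of entry, made twice. Mixed entry also suits the main aim, since section 11 attributes working-memory and processing-speed deficits to both disorders and the intervention targets working memory. Section 13 refers to appended intake procedures, not available for this review, which might record diagnosis or narrow entry.

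Much of this stands. It limits the consequence, but it does not make sections 11, 12 and 13 agree, and narrower intake forms would themselves conflict with section 13.

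A reader might infer four stronger things that the protocol does not support:

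- *That LD-only students weaken the whole trial.* The dilution argument concerns the ASRS, one far-transfer scale serving one of six objectives. It does not carry over to the working-memory measures.
- *That restricting the ASRS analysis to students with ADHD always gains power.* That holds only if LD-only students gain little, and it reverses at half the benefit.
- *That the restricted set should be the main ASRS analysis.* Section 22 aims at intent-to-treat, and Methods says the prior diagnoses rest on no standardized assessment.
- *That unstratified allocation biases the result.* Chance imbalance under randomisation is noise, not bias, and the ASRS is measured at baseline.

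Model terms and analysis sets are commonly left to a statistical analysis plan, and none was available here. Their absence from the protocol is not held against it.

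**Conclusion.** The point holds as an inconsistency about who is enrolled. As section 13 is written, LD-only and ADHD-only students both qualify, so the results would not apply specifically to the comorbid population of the rationale, and the test of objective v includes students not selected for ADHD symptoms.

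Dilution of the ASRS effect is conditional on LD-only students benefiting less. Its size cannot be derived from the protocol. Under the assumptions above, the loss from 79% power is anywhere from 9 points (20% LD-only, half the benefit: 79 − 70) to 51 points (50% LD-only, no benefit: 79 − 28). The figures show a range, not an estimate, and the baseline-adjusted model behind them is more favourable than the planned repeated measures ANOVA.

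This should be settled before randomisation, because stratification cannot be added afterwards.

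**What to change.** State one population and use it in the rationale, objectives, Methods and section 13, including the label for the randomised arms.

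If entry on either diagnosis is kept:

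1. Word the objectives and the intended conclusions for that mixed population.
2. Record diagnosis at intake as ADHD only, LD only, or both.
3. Stratify randomisation on it and include it as a model term.
4. Keep all randomised participants as the main ASRS analysis, and prespecify a supporting analysis in those with an ADHD diagnosis.

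The cost is wording, one stratification factor built on a diagnosis already required for entry, and one extra analysis. That analysis has a smaller n (for example 27 per arm if one-third are LD-only) and should be read accordingly.
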